### Statistical analysis plan

The statistical analyses will be the following:Analyses will be performed in accordance with the intention-to-treat principle and will take into account patients lost to follow-up.A two-sided significance level of 0.05 will be applied to both primary and secondary end-points.Unpaired *t* tests or Mann–Whitney *U* tests will be conducted for unpaired comparisons of numerical variables. A chi-squared or Fisher’s exact test will be conducted to examine differences between categorical variables.Association between LP ratio and “poor” neurological outcome (CPC 3–4) will be assessed with chi-squared test and logistic regression. The overall expected rates of unfavorable neurological outcome (CPC 3–4) are 5–7%, observed in earlier studies [34, 35]. The multivariate logistic model will be adjusted for time to ROSC, arterial carbon dioxide partial pressure, baseline LP, and average LP ratio > 30 > 24 and 48 h as covariates.Association between LP ratio and all-cause mortality will be assessed with chi-squared test and logistic regression.Receiver operating characteristic (ROC) curves will be constructed to determine the sensitivity and specificity of the LP ratio levels at each time point (and the maximal LP ratio level recorded during the ICU period) for predicting outcomes.Association between total duration (in minutes) of cerebral desaturation (rSO_2_ ≤ 50%) and unfavorable neurological outcome (CPC 3–4) and death will be assessed with chi-squared test and logistic regression.Time from start of randomization to death in the two blood pressure groups will be assessed by using the Kaplan–Meier method, and group differences will be tested by log-rank test. Cox regression will be applied for adjusted comparisons and estimation of hazard ratios.In regard to dynamic changes of MD variables in the two blood pressure groups, longitudinal models, applying linear mixed effects regression, will be used to account for repeated measurements of MD biomarkers across different patients over time.In regard to dynamic changes of blood pressure, longitudinal models, applying linear mixed effects regression, will be used to account for repeated measurements of blood pressure across different patients over time.

All standard assumptions regarding statistical models will be checked. Statistical analysis will be performed by using STATA V.15 (StataCorp LLC).

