**Methods/design:**

This is a single-center, randomized, double-blinded, superiority trial. Sixty unconscious patients with sustained return of spontaneous circulation after OHCA will be randomly assigned in a one-to-one fashion to low (63 mm Hg) or high (77 mm Hg) mean arterial blood pressure target. The primary end-point will be a difference in mean LP ratio within 48 h between blood pressure groups. Secondary end-points are (1) association between LP ratio and all-cause intensive care unit (ICU) mortality and (2) association between LP ratio and survival to hospital discharge with poor neurological function.

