### Sample size estimation

The sample size was calculated on the basis of the primary hypothesis but taking into account only the mean LP ratio and not the individual measurements; this was due to insufficient information about interpretation variation in LP values; this implies a conservative error and hence the true power of the study is expected to be higher than in this calculation. The trial is designed as a randomized study, and we have chosen to power this study according to differences in the LP ratio. A difference of 30% between groups is defined as the minimal clinically relevant difference. Assuming an average LP ratio of less than 20 over 48 h in the high MAP group compared with more than 35 over 48 h in the low MAP group, we will need to include 46 patients in total to achieve a power of 0.9 using a patient-to-patient variation with standard deviation (SD) of 15 in LP ratio as motivated by an earlier study [29] in the power calculation and assuming normal distribution of LP ratio. To take possible higher patient-to-patient variation in this study as well as deviations from normality into account, we plan to include at least 60 patients in total. Defining an LP ratio of more than 30 averaged over 24 and 48 h for both groups, we will analyze the proportion of patients reaching that end-point in each group.

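### Every secondary end-point is tested at the full two-sided 0.05 with no order, correction or exploratory label, so an isolated secondary p-value could be declared significant even after a null primary

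*Protocol article*

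**What the plan says.** The Statistical analysis plan section of the protocol article gives one rule on significance: "A two-sided significance level of 0.05 will be applied to both primary and secondary end-points".

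The End-points section lists five secondary end-points:

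1. the association of LP ratio with ICU mortality;
2. the between-arm difference in minutes of cerebral desaturation;
3. the between-arm difference in five jugular bulb metabolites (glucose, lactate, pyruvate, glycerol, glutamate);
4. the association of LP ratio with cardiac index;
5. the association of LP ratio with discharge in CPC 3–4.

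The three association analyses are to be adjusted for blood pressure group.

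Further analyses appear outside that list. The Sample size estimation section adds a dichotomised comparison: "Defining an LP ratio of more than 30 averaged over 24 and 48 h for both groups, we will analyze the proportion of patients". For time to death, the Statistical analysis plan says that "group differences will be tested by log-rank test", with Cox regression for adjusted comparisons, and it also plans ROC curves at each time point.

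None of these sections gives an order of testing, a requirement that the primary succeed first, an alpha split, a correction or an exploratory label.

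**The concern.** The article does not leave the significance level of the secondaries open. It fixes it, at the same value as for the primary. Someone following the plan could call any one of the secondary tests significant at the trial's declared level whatever the primary LP comparison showed.

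This matters because the primary is acknowledged to be a surrogate and the trial is small (60 patients, sized on LP ratio alone). With many other comparisons on offer, a chance finding on one metabolite or on desaturation time could be read as support for a pressure effect, and a chance association as support for the prognostic use of LP ratio. The article gives the reader no rule for discounting such a result.

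**Working it through.** **What the 0.05 level was budgeted for.** The article states no family-wise error rate, so there is none to reproduce. Its one design figure that depends on alpha is the sample size.

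- Inputs, all from Sample size estimation: "Assuming an average LP ratio of less than 20 over 48 h in the high MAP group compared with more than 35 over 48 h", so a difference of 15; an SD of 15; and "we will need to include 46 patients in total to achieve a power of 0.9".
- Normal approximation: n per arm = 2 × (1.960 + 1.282)² × 15²/15² = 21.0, rounded up to 22, or 44 in total.
- Exact two-sample t test: power is 0.8997 with 22 per arm and 0.912 with 23 per arm. So 23 per arm, 46 in total, reproduces the stated figure.

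The calculation therefore uses the full two-sided 0.05 for one LP comparison. That is in order, and the secondaries do not alter it.

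**Counting the secondary tests** (End-points section).

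- Between-arm: desaturation minutes (1) + metabolites (5) = 6.
- LP-ratio associations: ICU mortality, cardiac index, CPC 3–4 = 3.
- Total: 9.

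The LP>30 proportions, the comparison of death and the ROC curves are not listed as end-points, so they are left out of this count.

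**Chance of at least one p < 0.05 if all nulls are true.**

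- Independent tests: 1 − 0.95^k. For k = 9 this is 1 − 0.630 = 0.370. For k = 6 it is 1 − 0.735 = 0.265.
- Correlated tests: z_i = √ρ·W + √(1−ρ)·e_i, where W and e_i are independent standard normals, rejecting if any |z_i| > 1.96 (200,000 simulated draws). The article gives no correlations, so ρ is an assumption.

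| Tests | ρ = 0 | ρ = 0.5 | ρ = 0.9 |
|---|---|---|---|
| All nine listed secondaries | 0.37 | 0.27 | 0.12 |
| Six between-arm tests | 0.27 | 0.21 | 0.11 |
| Five metabolites | 0.23 | 0.18 | 0.10 |

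**Sensitivity to the correlation structure.** There is no clear reason for between-arm tests and arm-adjusted associations to share one correlation. If the six between-arm tests have ρ = 0.5 (0.208), and the three associations are independent of them and of each other (1 − 0.95³ = 0.143), the rate for all nine is 1 − 0.792 × 0.857 = 0.32. This lies inside the range in the first row.

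**The case against.** The strongest reply is that no promise is broken. The article sets a level for each end-point and never claims to control error across a family. Each test keeps its own 5%, and leaving supportive secondaries unadjusted is common in a small single-centre trial with a surrogate primary. This stands. A reader might infer that the trial's error rate is 27% when it was meant to be 5%. The documents do not support that, because it sets a family-wise rate against a per-test level, and the 27% depends on an assumed correlation. Nor do they support inferring that the primary comparison is compromised.

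A second reply is that the family is debatable. The between-arm tests and the LP associations serve different aims. Taking all nulls as true also sits oddly with the trial's premise that LP ratio marks poor outcome. This stands too, and it is why the six between-arm tests are shown separately. They still give 11% to 27%.

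A third reply is that an article leaves multiplicity to a fuller document. That would answer silence, but here the article states the rule. A fuller plan that called the secondaries exploratory would have to be squared with this sentence.

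Finally, the abstract names only two secondaries: "Secondary end-points are (1) association between LP ratio and all-cause intensive care unit (ICU) mortality and (2) association between LP ratio and survival" to discharge with poor neurological function. A reader might take this as a hidden ranking or as a multiplicity fault. It is better seen as abbreviation and is an editorial matter. The article's wording on prognosis is also tentative, and nothing in it says that a lone secondary result will be claimed as a trial finding.

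**Conclusion.** The point holds as a cheap improvement. The plan gives nine listed secondary tests the same declared significance level as the primary and offers no means of telling a supportive result from a confirmatory one.

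With all nulls true, the chance of at least one nominally significant secondary is about 12% to 37%, depending on an assumed common correlation of 0.9 down to 0. For the between-arm tests alone it is 11% to 27%. No single figure in these ranges is determinate. The conclusion does not need one, since even at a correlation of 0.9 an isolated significant secondary is more than twice as likely as for a single test. The point does not touch the primary comparison or the sample size.

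**What to change.** Replace the sentence on significance level in the Statistical analysis plan with:

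> The two-sided 0.05 level applies to the primary end-point. Secondary end-points, the LP>30 proportions, the log-rank and Cox comparison of death, and the ROC analyses are exploratory and are reported as estimates with 95% confidence intervals, without claims of statistical significance.

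If p-values for the five metabolites are nevertheless to be interpreted, apply Holm within that group (first step 0.05/5 = 0.01).

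Do not make the LP–outcome associations conditional on a significant primary. LP ratio could predict outcome whether or not the arms differ. A fixed sequence led by the CPC 3–4 end-point would also rest on very few events: the article expects 5–7%, and 0.05 × 60 = 3 to 0.07 × 60 = 4.2, so about 3 to 4 patients.

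The cost is one or two sentences, with no new data or patients. The downside is that an isolated secondary p-value below 0.05 can no longer be called a significant result of the trial.

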### End-points

The study focuses on the following end-points:

Primary end-pointComparing mean LP ratio differences within 48 h between blood pressure groups and comparing individual LP ratio measurements using longitudinal analysis.

Secondary end-pointsAssociation between LP ratio and all-cause mortality during ICU stay adjusted for blood pressure groupsBetween-group difference in total duration (minutes) of cerebral desaturation defined as an absolute rSO_2_ of not more than 50% during ICU stayBetween-group difference within 48 h in lactate, pyruvate, glutamate, glycerol, and glucose measured in jugular bulbAssociation between LP ratio and cardiac index adjusted for blood pressure groupsAssociation between LP ratio and survival to hospital discharge with poor neurological function (CPC 3–4) adjusted for blood pressure groups.

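### The multivariable logistic model for CPC 3–4 has four to six terms for about three to four expected events, omits the blood pressure group its end-point requires, and does not identify one LP exposure.

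*Protocol article*

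**What the plan says.** The last secondary end-point in the End-points section is the association between LP ratio and survival to discharge with "poor neurological function (CPC 3–4) adjusted for blood pressure groups". The abstract names it as one of two secondary end-points, and it serves aim (c), the link between LP ratio and CPC.

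The Statistical analysis plan assigns this association to a chi-squared test and logistic regression. On frequency it says: "The overall expected rates of unfavorable neurological outcome (CPC 3–4) are 5–7%, observed in earlier studies". On the model it says: "The multivariate logistic model will be adjusted for time to ROSC, arterial carbon dioxide partial pressure, baseline LP, and average LP ratio". The sentence then adds a threshold of 30 and the times 24 and 48 h in a garbled expression, and calls all of these covariates. Blood pressure group is not in the list. No penalised, exact or reduced model is named for sparse events.

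On size, the Sample size estimation section says: "we plan to include at least 60 patients in total". It also defines an LP ratio above 30, averaged over 24 and 48 h, as a measure whose proportion is to be compared between groups.

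**The concern.** The article supplies both the expected event rate and the covariate list, and the two do not fit together. A logistic model with about one event per term or fewer is prone to separation, where no finite maximum-likelihood estimate exists. When it does converge, the estimates are unstable and biased away from zero.

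There are two further problems of specification. The end-point asks for adjustment for blood pressure group and the list does not include it. This matters because the trial's hypothesis is that the group changes the LP ratio. LP also appears as baseline LP and as a thresholded average over two windows, so the reader cannot tell which coefficient answers the question.

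At stake is the trial's own evidence on whether LP relates to neurological outcome in this population. The Surrogate end-point section otherwise supports that link from traumatic brain injury studies.

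**Working it through.** **Plan's own figure first.** Inputs from Sample size estimation: "Assuming an average LP ratio of less than 20 over 48 h in the high MAP group compared with more than 35 over 48 h" with the lower target, so a difference of 15; "standard deviation (SD) of 15 in LP ratio"; power 0.9; 1:1 allocation. From the Statistical analysis plan: "A two-sided significance level of 0.05 will be applied to both primary and secondary end-points". The normal approximation gives 22 per arm, 44 in total. With the noncentral t distribution, 44 patients give power 0.8997 and 46 give 0.912. The article's statement, "we will need to include 46 patients in total to achieve a power of 0.9", is therefore reproduced. This calculation concerns the primary end-point only; the article gives no event count for the logistic model.

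**Expected CPC 3–4 events** = patients × rate.
- 60 × 0.05 = 3.0
- 60 × 0.07 = 4.2

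**Events per term** = expected events / number of model terms.

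| Reading | Terms | At 5% | At 7% |
|---|---|---|---|
| Listed covariates, LP above 30 as one item | 4 | 3.0/4 = 0.75 | 4.2/4 = 1.05 |
| Listed covariates, 24 h and 48 h separate; or one LP item plus group | 5 | 3.0/5 = 0.60 | 4.2/5 = 0.84 |
| 24 h and 48 h separate, plus group | 6 | 3.0/6 = 0.50 | 4.2/6 = 0.70 |

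A separate LP exposure on top of these would add a further term; it is not counted here.

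**Spread of the event count** (binomial, 60 patients):
- four or fewer events: 82% at a 5% rate, 59% at 7%
- no events: 4.6% and 1.3%
- ten or more events: below 1% at either rate

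**If the 5–7% applied to survivors only.** This is an assumption. With the 30–50% in-hospital mortality in the Background, 30–42 of 60 survive, and 30 × 0.05 = 1.5 to 42 × 0.07 = 2.9 events are expected.

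**Can the model be fitted?** In 1,000 simulated trials per setting (60 patients, no true effects, assumed correlations among the LP measures, separation tested by linear programming), ordinary maximum likelihood was not estimable, through zero events or separation, in:
- five terms: 48% at a 5% rate, 31% at 7%
- six terms: 59% at a 5% rate, 38% at 7%

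These percentages move with the assumed correlations and the share of patients above the threshold. The events-per-term figures do not.

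**End-point against covariate list.** The end-point requires adjustment for blood pressure group; the list has time to ROSC, arterial carbon dioxide, baseline LP and LP above 30 at 24 and 48 h, with no group term.

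**LP terms.** The 48 h average contains the first 24 h, so the two indicators overlap if both enter one model, and the text does not say whether they do.

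**What a two-term model would have.** One LP exposure plus group: 3.0/2 = 1.5 to 4.2/2 = 2.1 events per term. This is still sparse.

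**What CPC 3–5 would have.** Adding deaths under the Background's 30–50% mortality: 60 × (0.30 + 0.05) = 21 to 60 × (0.50 + 0.07) = 34.2 events. The smaller class limits the model: 21/3 = 7 per parameter at the low end, 25.8/3 = 8.6 at the high end, and at most 30/3 = 10 in between, with three parameters.

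**The case against.** The strongest reply accepts the event count and contests the rest.

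- **LP adjusted for itself.** A reader might infer that the model estimates LP given LP. The documents do not establish this. The expression is garbled, and Sample size estimation treats LP above 30 over 24 and 48 h as a defined LP measure. It can be read as the exposure loosely called a covariate, with baseline LP as an ordinary adjustment. The 24 h and 48 h versions may also be alternatives rather than joint terms. What stands is that no single LP exposure is identified.
- **Missing group.** Read together, the two sections can be taken as group plus the listed covariates, so one phrase would harmonise them. That is fair. It does not help with sparsity, because the count is too low with or without the group.
- **Unanswerable end-point.** A reader might infer that the LP–outcome question is lost altogether. It is not: a chi-squared test and ROC curves are also planned, so an unadjusted description remains. The adjusted estimate named in the end-point is what cannot be relied on.
- **Unseen full plan.** Fallback methods for sparse events may sit in a document not shown, so their absence alone is not the fault. The fault is that the article itself fixes a list that its own event rate cannot support and that disagrees with its own end-point.
- **Changing the outcome.** Replacing CPC 3–4 by CPC 3–5 would be an end-point change, with deaths forming most of the events and overlapping the mortality analysis. This stands, and the fix below keeps CPC 3–4.

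**Conclusion.** The concern holds in this form. With 60 patients and the article's own 5–7% rate, about three to four CPC 3–4 events are expected against four to six terms: 0.5–1.05 events per term over all readings, and 0.5–0.7 with six. Ordinary logistic regression would often fail, in roughly 30–60% of trials in simulations that are illustrative only. The omission of blood pressure group is an inconsistency between two sections of the current text, and the LP exposure needs to be named.

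The event figures rest on the stated rate applied to all 60 patients; applied to survivors only, they would be lower. Recruiting somewhat more than 60 would not change the conclusion: ten events per term, as a benchmark, would need 715–1,000 patients for five terms and 858–1,200 for six.

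The randomised comparison, the primary end-point and the sample size are unaffected. This should be fixed, but it is not a fault in the trial's main result.

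**What to change.** For the CPC 3–4 end-point:

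1. Name one LP exposure, for example continuous mean LP over one stated window.
2. Fit it with blood pressure group only, by Firth-penalised or exact logistic regression.
3. Drop the other LP terms, time to ROSC and arterial carbon dioxide from this model.
4. Report LP above 30 at 24 h and at 48 h in separate unadjusted tables.
5. State that the estimate is exploratory and imprecise. Penalisation gives finite estimates but adds no information.

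Optionally, add CPC 3–5 versus 1–2, labelled as an additional outcome and not a replacement. It would support about three parameters, at roughly 7–10 per parameter if the Background's mortality range applies.

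The cost is a change of analysis wording and less adjustment for confounders in a non-randomised association. The optional outcome would need to be declared as an addition. No change to recruitment or data collection is needed.

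### The LP–outcome associations are tested by both chi-squared and logistic regression with neither named as decisive, and as written neither delivers the blood-pressure-group adjustment that the end-points require

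*Protocol article*

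**What the plan says.** The statistical analysis plan in the protocol article gives three associations the same pair of methods.

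- LP ratio and mortality: "Association between LP ratio and all-cause mortality will be assessed with chi-squared test and logistic regression".
- LP ratio and poor neurological outcome: the same two methods, with the note "The overall expected rates of unfavorable neurological outcome (CPC 3–4) are 5–7" per cent.
- Desaturation: "Association between total duration (in minutes) of cerebral desaturation" against CPC 3–4 and against death, again by both methods.

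The same section states: "A two-sided significance level of 0.05 will be applied to both primary and secondary end-points". It does not rank the two tests.

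The End-points section lists LP ratio with ICU mortality, and LP ratio with survival to discharge at CPC 3–4, as secondary end-points. Each is adjusted for blood pressure group. The one covariate list, given with the CPC 3–4 analysis, reads: "The multivariate logistic model will be adjusted for time to ROSC, arterial carbon dioxide partial pressure, baseline LP, and average LP ratio" above 30 at 24 and 48 h. Blood pressure group is not in it. No covariates are listed for the mortality model.

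On thresholds, the sample size section says: "Defining an LP ratio of more than 30 averaged over 24 and 48 h for both groups, we will analyze the proportion of patients" reaching it in each group.

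**The concern.** The analysis named for the two LP–outcome end-points does not match their definition. A plain chi-squared test is unadjusted. The logistic model could adjust, but its only stated covariates leave out the variable that the end-point names.

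A chi-squared test also needs categories, whereas LP ratio and desaturation minutes are continuous. Splitting them discards information and leaves open where to split and, for LP, over which window.

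With two tests per association and no decisive one, either could be reported as the result. At stake are the false-positive rate and the meaning of the LP–outcome claims, which support the article's argument that jugular bulb LP ratio has prognostic value.

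**Working it through.** **The plan's own figure first.** The sample size section assumes LP means of 20 and 35 (difference 15), SD 15 and power 0.9. The normal approximation gives 2 × (1.960 + 1.282)² × (15/15)² = 21.02, so 22 per arm or 44 in total. Exact t-test power is 0.8997 at 22 per arm and 0.912 at 23 per arm, so the smallest total reaching 0.90 is 46. The stated 46 reproduces and is not in dispute.

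**Reference value for two tests.** If two tests at 0.05 were independent, the chance that at least one is significant under no association would be 1 − 0.95² = 0.0975. Tests on the same data are correlated, so the true value is lower and has to be simulated.

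**Simulation under no LP effect.** The inputs were:
- 60 patients, 30 per arm, LP normal with SD 15 (sample size section);
- arm means of 35 and 20, or 27.5 in both arms (no arm effect on LP, an added scenario);
- death independent of LP and arm at 30, 40 or 50%. The Background gives 30–50% for in-hospital mortality; using it for ICU mortality is an assumption.

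The tests were Pearson chi-squared on LP > 30, and a likelihood-ratio test of continuous LP in a logistic model with blood pressure group. Each row has 5,000 runs. The Monte Carlo standard error near 9% is √(0.09 × 0.91/5000) ≈ 0.4 percentage points.

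| LP means, low/high MAP | Mortality | Chi-squared alone | Adjusted logistic alone | Either significant |
|---|---|---|---|---|
| 35/20 | 30% | 4.6% | 5.8% | 8.8% |
| 35/20 | 40% | 4.8% | 5.4% | 8.5% |
| 35/20 | 50% | 5.1% | 5.1% | 8.7% |
| 27.5/27.5 | 30% | 5.4% | 6.1% | 8.7% |
| 27.5/27.5 | 40% | 5.6% | 6.1% | 9.3% |
| 27.5/27.5 | 50% | 5.4% | 6.1% | 8.9% |

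Each test alone is close to nominal. The excess comes from having two.

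**Effect of not adjusting.** Keep LP means at 35/20 and no LP effect within arm, but let mortality differ by arm (contrasts assumed, not in the documents):
- 50% low MAP, 30% high MAP: chi-squared rejects in 9.5% of runs, adjusted logistic in 5.9%.
- 45% low MAP, 35% high MAP: 5.7% and 5.4%.

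**Events for CPC 3–4.** 60 × 0.05 = 3.0 and 60 × 0.07 = 4.2. Under the planning means, P(LP > 30) is Φ(5/15) = 0.63 in the low arm and 1 − Φ(10/15) = 0.25 in the high arm, about 0.44 overall. Expected events are then 3.0 × 0.44 = 1.3 to 4.2 × 0.44 = 1.8 above the threshold, and 3.0 × 0.56 = 1.7 to 4.2 × 0.56 = 2.4 below it. That is too few for a chi-squared approximation. The listed covariates make four terms, or five if the two LP windows enter separately, against 3–4 events.

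**The case against.** A crude test followed by a model is a common layout, the end-points are secondary, and a condensed article may leave detail to a fuller plan. Several stronger readings also fail.

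- *LP has no cut-point.* It has one: above 30, over 24 and 48 h, in the sample size section and again in the covariate list. What is missing is the link to the chi-squared tests and the choice of window. Only desaturation minutes have no cut-point at all.
- *Cut-points will be searched for in the data.* Taking the best of nine decile cuts would push the either-test rate to 24–27%, but the article proposes no such search for these tests.
- *The unadjusted test is biased because arm shifts LP.* Confounding also needs an arm effect on mortality. Without one, chi-squared alone holds its level.
- *Small cells are ignored.* The analysis plan allows Fisher's exact test for categorical variables in general. The line for CPC 3–4 names only chi-squared, but a remedy is at hand. It does not cure the shortage of events for the logistic model.
- *No adjustable method exists.* Logistic regression is named each time and can carry blood pressure group.

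In addition, desaturation against outcome appears only in the analysis plan, not among the listed end-points, so the 0.05 rule is not expressly attached to it.

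What stands is a mismatch stated in the text, not an omission left to another document. The end-points require group adjustment, one named test cannot give it, the other's only covariate list omits it, and neither is decisive.

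**Conclusion.** The point holds for the secondary LP–outcome associations and for the desaturation–outcome analyses. If significance on either test counts, the false-positive rate is about 9% (8.5–9.3%), against 5.1–6.1% for the group-adjusted logistic model alone. This rests on normal LP with SD 15, 60 patients, mortality of 30–50%, a chi-squared split at 30 and LP continuous in the logistic model. If the logistic model used the same LP > 30 indicator, the two tests would overlap more and the excess would be smaller.

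Confounding of the chi-squared test adds to this only if arm also changes mortality: 9.5% for that test alone at an assumed 50% versus 30%, and little at 45% versus 35%. For CPC 3–4, 3–4 events support neither a chi-squared test nor the listed multivariable model.

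A reader might infer that the primary comparison or the sample size is compromised. Neither is: both rest on mean LP ratio by arm, and the 46 reproduces. The change is worth making but not critical.

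**What to change.** For each association, name one logistic regression as the sole inferential test. Enter LP ratio as a continuous term over one stated window, or desaturation minutes as a continuous term on a suitable scale, with blood pressure group as a covariate. Add group to the covariate list, so that the analysis matches the End-points section.

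For CPC 3–4, use a penalised or exact version with the fewest covariates that meet the definition: LP ratio and group.

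Keep cross-tabulations as description without p-values, using LP > 30 over one stated window. If desaturation minutes are tabulated, fix the cut-point in advance.

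This changes analysis wording only, with no effect on data collection, sample size or the primary analysis. What is lost is the simple 2×2 p-value.
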